**Investigational medicinal product and placebo:**

**Intervention for Arms 1, 2, 3, 4 and 5 (PVP-I group/treatment group):** Arm 1 will receive povidone iodine (PVP-I) nasal irrigation at a concentration of 0.4%, Arm 2 will receive povidone iodine (PVP-I) nasal irrigation at a concentration of 0.5%, Arm 3 will receive povidone iodine (PVP-I) nasal irrigation at a concentration of 0.6%, Arm 4 will receive PVP-I nasal spray at a concentration of 0.5% and Arm 5 will receive PVP-I nasal spray at a concentration of 0.6%. The contact time will be minimum 30 seconds.

**Intervention for Arms 6 and 7 (placebo comparator):** Arm 6 (Placebo comparator group) will receive nasal irrigation with distilled water, and Arm 7 (Placebo comparator group) will receive nasal spray with distilled water for the same duration as a placebo agent.

All groups of patients will receive standard medical care according to country guideline.

**Preparation of placebo:** As this study will be an open label study, no blinding will be performed and no dummy placebo will be made.

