**Patients and Methods:** This open-label randomized clinical trial will be conducted at the Department of Otorhinolaryngology and Head Neck Surgery in collaboration with the Department of Virology and Department of Medicine in Dhaka Medical College Hospital (DMCH). The study will be conducted from September 2020 to December 2020. A total of 189 confirmed cases of COVID-19 disease proven by reverse transcription polymerase chain reaction (RT-PCR) testing will be enrolled in this study. Written informed consent will be ensured before participation. In case of no literacy, fingerprint will be considered for written permission. Consent will be sought from the legal guardian in case of minor or underaged. Formal ethical clearance will be obtained from the Ethical Review Committee (ERC) of Dhaka Medical College (DMC). All of the participants will be divided into seven Arms: Arm 1 will receive povidone iodine (PVP-I) nasal irrigation at a concentration of 0.4%, Arm 2 and Arm 3 will receive 0.5% and 0.6%, Arm 4 will receive PVP-I nasal spray at a concentration of 0.5% and Arm 5 will receive 0.6%. Arm 6 (placebo comparator group) will receive nasal irrigation with distilled water (DW), and Arm 7 (placebo comparator group) will receive nasal spray with distilled water. The contact time will be minimum 30 seconds. After the individual application of PVP-I and distilled water in the respective participants, they will be tested again for RT-PCR for COVID-19 from nasopharyngeal samples. All patients will be subjected to a detailed history, physical examination and adverse events. Computer generated randomization sequence will be followed for randomization. Data will be recorded in a semi structured questionnaire and will be analyzed by ‘R-4.0.2’ data analysis software.

**Conclusion:** It is expected that the study will reveal the virucidal activity with optimal contact time and concentration of nasal preparations of PVP-I against COVID-19. The results may help in prevention strategies for the general population, health care workers and COVID-19-positive patients.

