**METHODOLOGY**

**Study Design:** Open label randomized clinical trial.

**Place of Study:** Department of Otorhinolaryngology and Head Neck Surgery, in collaboration with Department of Virology and Department of Medicine, Dhaka Medical College Hospital, Dhaka, Bangladesh.

**Period of study:** The study period will be September 2020 to December 2020.

**Study population:** Confirmed cases of COVID-19 disease proven by RT-PCR testing.

**Sampling and statistical basis of the sample size:** The sample size was determined using the following formula:

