**Dosing regimen:**

**Intervention Arms (Arms 1, 2, 3, 4, 5):** Participants allocated to PVP-I solution (especially prepared for the study) after confirmation of COVID-19 positivity. Proper dilution with normal saline will be added, which will be physically and chemically stable for 6 hours. Other supporting care (crystalloid solution infusion), and monitoring of vital statistics, in case of bleeding protective measures will be performed according to the national guidelines.

**Control Arms (Arms 6 and 7):** Participants allocated distilled water for nasal irrigation for Arm 6 a placebo that will also be reconstituted and applied at the same rate as mentioned in the invention groups and distilled water for nasal spray for Arm 7 a placebo that will also be reconstituted and applied at the same rate as mentioned in the invention groups.

In both Arms of patients, 10 ml of PVP-I or distilled water will be administered for 2 minutes. Nasal spray will be administered in each nostril using an atomizing device (2 sprays for average device). Control groups, will receive distilled water irrigation and distilled water nasal spray at similar amounts and durations. Further RT-PCR will be assessed within 1 minutes to 15 minutes of the following intervention.

**Participant compliance:** The study team will not create any problem with compliance while the patient is under care and supervision in the hospital. It will be ensured that all recruited patients will receive the appropriate interventions, although they could be interrupted due to the onset of potential adverse effects such as hypotension.

**Overdose:** The study team will titrate the drugs against the key adverse effect of hypotension. Nasal spray and nasal irrigation will be halted if patients complain of significant discomfort or clinically significant hypotension or signs of anaphylaxis. Procedures will be started again at a lower rate if the condition settles or according to the patient’s choice.

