**Responsibility sharing of care of the patients:** As the patients will remain under the care of the hospitals’ consultant physicians/unit head who will have primary responsibility for their management. Management protocols will be agreed upon between the medical team and study team. Decisions about intubation, requirement of blood and blood products, transfer of patients to intensive care, weaning of ventilation and extubation will be made by the medical team independently of study doctors. All decisions will be based on the patient’s clinical condition and the available hospital resources, as per usual hospital practice. The study team preferably by trial physicians will note down the record in the patient’s case record form (CRF).

**Prohibited Medications:** No medicines are specifically prohibited for this clinical trial.

**Non-investigational medicinal products:** All patients will receive standard care plus supporting care according to the “National Guidelines on Clinical Management of Coronavirus Disease 2019 (COVID-19)”. Among the standard care fluids, oxygen, ventilatory support, and antipyretics will be provided as necessary in all Arms of patients and will be decided by the chief/consultant of the admission unit. No other noninvestigational product will be used for the study purpose. In case of any product required for the best suited management, inclusion of this patient will be decided upon the opinion of the PI.

**Methods of data collection:** Data collection will be performed by the trial physicians. A paper based semi-structured questionnaire will be made and pretested before data collection. All potential participants will be recorded in this database at first contact and assigned a study number. This study number (e.g., DMC-PVP-I-0001) will be used for all data and samples collected from that person. Study doctors will recruit and randomize patients. They will not be able to predict allocation before randomization. Following randomization, allocation will be performed by the PI, and trial physicians or nurses will confirm the administration of either drug (0.4% or 0.5% or 0.6% PVP-I)/placebo (distilled water). Patients will be closely monitored. Temperature will be measured every 6 hours, and blood pressure, respiratory rate, and pulse rate will be measured every hour. Urine output will be measured in every 8 hours. Drug-related side effects or any adverse events will be observed in each group.

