If there is no reaction or unusual event, another RT-PCR sample will be collected from the nasopharynx and sent for further testing.

The total duration of the follow-up will be 2 days (or a person fulfills the discharge criteria). All clinical events will be noted in case record form by trial physicians, including vital status at hospital discharge. Data entry will be date/time stamped. Laboratory analysis data will be collected using the same CRF.

**Data quality and standards:** Following collection, all data sets and collected record forms will be checked. A formal clinical data management plan will be written before the study starts, agreed upon by the co-investigators and Data Monitoring Committee, and documented as a trial master file. Laboratory results will be discussed regularly between the PI and laboratory managers.

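### The protocol rules out blinding without excepting the laboratory that reads the post-treatment RT-PCR, so knowledge of the arm is not excluded from the efficacy result

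*Protocol*

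**What the plan says.** Under Investigational medicinal product and placebo, in the paragraph on preparation of placebo, the protocol says "As this study will be an open label study, no blinding will be performed and no dummy placebo will be made". The Methodology section gives the design as "Open label randomized clinical trial".

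The efficacy reading is a second nasopharyngeal RT-PCR. The summary says of participants after treatment that "they will be tested again for RT-PCR for COVID-19 from nasopharyngeal samples", and the dosing section adds "Further RT-PCR will be assessed within 1 minutes to 15 minutes of the following intervention". The text on data collection says that, absent a reaction, "another RT-PCR sample will be collected from the nasopharynx and sent for further testing".

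Three further statements bear on who can know the arm:

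- Methods of data collection: "allocation will be performed by the PI, and trial physicians or nurses will confirm the administration".
- The same section, on labels: "This study number (e.g., DMC-PVP-I-0001) will be used for all data and samples collected from that person".
- Data quality and standards: "Laboratory results will be discussed regularly between the PI and laboratory managers".

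The Department of Virology is named as a collaborating department. No section masks the person who takes the swab, runs the assay, decides on a rerun or calls the result.

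**The concern.** An open-label design is a reason not to mask patients and the staff who give the treatment. It is not a reason to leave the laboratory unmasked. The blinding sentence makes no such distinction, and nothing else in the protocol supplies it.

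An RT-PCR result is fairly objective, but not wholly so: a result near the detection limit has to be called, and someone decides whether to accept or rerun a failed or doubtful test. The protocol gives no rule for either. If the person deciding knows the arm and shares the trial's expectation, errors will tend to favour PVP-I. With 27 patients per arm, a shift of a few results in one arm can move a comparison across the 5% line. The protection cannot be added once samples have been read.

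**Working it through.** **Is the laboratory masked anywhere?**

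| Question | What the protocol gives |
|---|---|
| Is blinding stated? | Ruled out, with no exception (preparation of placebo) |
| Is the laboratory or result caller masked? | Not stated in any section |
| Who knows the arm? | The PI, who allocates; the physicians or nurses who confirm administration |
| Can the PI link patient to arm? | Yes: the PI hands over envelopes numbered to match enrolment numbers (Procedure of randomization) |
| Does the PI speak to the laboratory about results? | Yes, regularly, with no masking condition (Data quality and standards) |
| What does the sample label show? | A study number; the example carries no arm code |
| Are laboratory staff told the arm? | Not stated |

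So the person who holds the allocation is in regular contact with those responsible for the results, and no rule keeps the arm out of that contact. The study number is a partial safeguard. It is not described as masking, and it does not govern what is said in those discussions.

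**Does any planned figure change?** No. The sample-size inputs are σ = 10, difference 5, Z = 1.96 and 0.84, r = 1. They give 2 × (1.96 + 0.84)² × 10² / 5² = 62.72, so 63 per group and 126 in total, as stated. Then 126 + 60 = 186, 186 / 7 = 26.6, rounded up to 27, and 7 × 27 = 189. Laboratory masking enters none of these steps.

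**How many calls would matter?** Inputs: 27 per arm (protocol), and a positive/negative result compared by Pearson chi-square without continuity correction (assumed; the analysis plan lists chi-square among its tests). Suppose 5 of 27 control results are negative:

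- 11 of 27 negative in a PVP-I arm: X² = 54 × (5×16 − 11×22)² / (27 × 27 × 16 × 38) = 3.20, p = 0.074.
- 12 of 27: X² = 54 × (5×15 − 12×22)² / (27 × 27 × 17 × 37) = 4.21, p = 0.040.

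Seven extra negatives are therefore needed if every other result is equal. For 0 to 13 control negatives, the number needed is 4 to 8 by chi-square and 6 to 9 by Fisher's exact test.

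**What would arm-aware calls do to the error rate?** This is an illustration. The true negativity of 20% in all arms and the size of the shift are assumptions with no source in the documents. The rate is the sum, over all pairs of counts, of the product of the two binomial probabilities wherever X² exceeds 3.84.

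| Called negative, PVP-I v water | 27 v 27 | 135 v 54 |
|---|---|---|
| 20% v 20% (no shift) | 0.057 | 0.047 |
| 25% v 20% (5 points, PVP-I only) | 0.080 | 0.100 |
| 30% v 20% (10 points, PVP-I only) | 0.146 | 0.273 |
| 25% v 15% (5 points each way) | 0.163 | 0.307 |
| 30% v 10% (10 points each way) | 0.487 | 0.876 |

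Here 135 = 5 × 27 and 54 = 2 × 27. Five points is 0.05 × 27 = 1.35 results per arm. Ten points each way is 0.10 × 189 = 18.9 miscalled results across the trial, every one favouring PVP-I.

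**The case against.** The strongest reply is that the sentence means less than it seems to. It stands under preparation of placebo and can be read as explaining only why no matched product is made. No section says that laboratory staff learn the arm, samples travel under a number whose example shows no arm, and RT-PCR leaves limited room for judgement. The discussions between the PI and the laboratory stand under a data-quality heading, are with managers and not with those reading results, and are not said to be by arm or even about the outcome RT-PCR. The data management plan, promised before the study starts, may cover result handling.

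Most of this stands, and it limits the point. A reader might infer that the laboratory is in fact unmasked and that its readings will be biased; the documents do not support that. A reader might also take the larger error rates above as the expected damage. They require errors in both directions at once, at rates the documents do not give. The illustration further assumes a positive/negative outcome. Wording about clearing the virus suggests one, but the sample size uses a continuous outcome, and the t test and ANOVA are listed beside chi-square.

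What the reply does not do is point to any passage that masks the laboratory. The sentence is unqualified, and the PI's two roles meet with no rule between them.

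Calling Arms 6 and 7 placebo comparators while making no dummy placebo is loose wording. Changing it is optional and alters no result; it is not part of this point.

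**Conclusion.** The point holds in a limited form. The protocol rules out blinding and makes no exception for the laboratory that reads its efficacy test, while the PI who allocates also discusses laboratory results with the laboratory managers. Knowledge of the arm is therefore not excluded from borderline calls or reruns. It is not shown to be present.

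The size of any bias cannot be derived from the documents. On the assumptions above, the illustrative false-positive rate runs from 8% (5-point shift in PVP-I only, 27 v 27) to 88% (10 points each way, 135 v 54). The range mainly shows how strongly the answer depends on an unknown miscall rate. The case for changing the text rests on the very low cost of masking here, not on any one of these figures.

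**What to change.** 1. In the paragraph on preparation of placebo, state that patients and administering staff are not masked, but that laboratory staff and laboratory managers are masked to arm; that samples reach them under the study number only; and that result calls and reruns follow the assay rule and are locked before they are linked to allocation.
2. Under Data quality and standards, limit discussions between the PI and the laboratory to assay quality, such as failed runs and controls, without reference to arm.

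The cost is wording. The samples already carry study numbers, and no patients, tests or staff are added. There are two small drawbacks. The PI could not discuss individual results by arm while the trial runs. The masking is also partial, because whoever takes the swab minutes after treatment may know the arm.

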### Storage:

Drugs will be stored at room temperature 20-25^0^ in a trial storage room. The reconstituted solution will also be kept at temperatures of 20-25^0^. Solution should be used within 48 hours after mixing. The trial storage room will be monitored, and the logging of temperatures will be noted. Drugs will be transported by the manufacturers to the study sites using their standard temperature-controlled processes.

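### The protocol lets PVP-I solution be used up to 48 hours after mixing, gives 6 hours as its sole stability figure, and does not say whether both limits concern the same preparation

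*Protocol*

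**What the plan says.** Two operative sections of the protocol give a time limit for the study solution.

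- **Storage:** "The reconstituted solution will also be kept at temperatures of 20-25^0" degrees, followed by "Solution should be used within 48 hours after mixing".
- **Dosing regimen, intervention arms:** "Proper dilution with normal saline will be added, which will be physically and chemically stable for 6 hours".

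The section on the investigational product fixes the concentrations by arm. Irrigation is at 0.4%, 0.5% and 0.6% in Arms 1 to 3. Spray is at 0.5% and 0.6% in Arms 4 and 5. The conclusion of the Part-A summary expects that "the study will reveal the virucidal activity with optimal contact time and concentration of nasal preparations of PVP-I against COVID-19".

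**The concern.** Concentration is what distinguishes the PVP-I arms within each route, so the arm label should describe what the participant received. A site that follows the Storage section to the letter can give solution well past the period for which the Dosing regimen section vouches for it. The protocol cites no stability data from 6 to 48 hours and no check of concentration at use. It logs the temperature of the storage room but mentions no record of the solution's age when applied.

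Two things are at stake. The first is product handling, because the protocol does not say which limit governs the solution given to the patient. The second is interpretation. If solution loses strength with age, and age varies from one participant to the next, the concentration received will vary around or below the label in arms that sit close together. With 27 participants in each of five PVP-I arms, 5 × 27 = 135 participants would receive product under these instructions.

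**Working it through.** **Inputs.** Use window 48 h (Storage). Stated stability 6 h (Dosing regimen). Concentrations 0.4/0.5/0.6% by irrigation and 0.5/0.6% by spray (Investigational medicinal product and placebo). The protocol gives no loss rate, so there is no figure of its own to reproduce.

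**Step 1: the gap between the limits.**
- Ratio: 48 / 6 = 8.
- Hours without a stated stability: 48 − 6 = 42, which is 42 / 48 = 87.5% of the permitted window.

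**Step 2: do the sections refer to different preparations?** Storage speaks of a reconstituted solution and of time since mixing. Dosing regimen speaks of a specially prepared PVP-I solution and a dilution in saline. The same section says that the distilled-water placebo will also be reconstituted, which suggests the word is used loosely for whatever is made ready for use. No sentence separates a stock solution from a final dilution, or attaches one limit to each. The text leaves the question open.

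**Step 3: how much loss would matter?** The relative loss that takes one concentration to the next lower label is:
- 0.6% to 0.5%: (0.6 − 0.5) / 0.6 = 16.7%
- 0.5% to 0.4%: (0.5 − 0.4) / 0.5 = 20%

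**Step 4: the same loss in every arm.** At a common relative loss of 16.7% (multiply by 5/6):
- 0.6 → 0.50, 0.5 → 0.42, 0.4 → 0.33

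Order and ratios are kept. The step shrinks from 0.10 to about 0.08 point, and the arms do not merge. A 0.6% solution meets a 0.5% solution only when the first is aged and the second is fresh, so what matters is variation in solution age.

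**Step 5: sensitivity under an assumed loss.** Assume first-order loss at a constant rate. If the loss at 6 h is L, the loss at 48 h is 1 − (1 − L)^8, because 48 / 6 = 8.

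| Assumed loss at 6 h | Loss at 48 h | 0.6% becomes | 0.5% becomes |
|---|---|---|---|
| 1% | 8% | 0.55% | 0.46% |
| 2% | 15% | 0.51% | 0.43% |
| 5% | 34% | 0.40% | 0.33% |
| 10% | 57% | 0.26% | 0.22% |

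Solving 1 − (1 − L)^8 = 16.7% gives L ≈ 2.3%, and solving for 20% gives L ≈ 2.8%. Under this model, a loss of that size at 6 h would bring a 48-hour-old solution down to the label of the next lower arm. The rates are assumptions. The table shows sensitivity and is not evidence that such loss occurs.

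**The case against.** The strongest reply is that the two sentences can both be obeyed: solution used within 6 hours is also used within 48. The Dosing regimen sentence does not say that the solution is unstable after 6 hours. A two-step preparation, with one limit for a prepared solution and the other for the final saline dilution, is also a plausible reading. This stands in part. It shows that the defect may lie in the wording and not in the product. But the person preparing the dose still cannot tell which limit governs it, and compliance with the Storage section alone permits use beyond the stated stability.

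A second reply is that the effect on the trial's main question is limited. The hypotheses and objectives ask whether PVP-I clears virus, the sample size is a two-group calculation, and optimal concentration appears only as an expectation in the Part-A conclusion. That is fair, and it limits the weight of the interpretive consequence. It does not remove the conflict in handling.

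A reader might infer that the PVP-I arms collapse into one another, or that patients would receive out-of-specification product. The document supports neither. It gives no loss rate and no product specification. The same storage and dilution text covers all PVP-I arms, and random allocation gives no reason to expect solution age to differ systematically between them. The case report form is not shown, so it cannot be said to lack mixing and application times. The protocol's date and time stamp concerns data entry and need not capture either.

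**Conclusion.** The inconsistency is real. The permitted use window is 8 times the one stability period stated, and up to 42 hours of use have no stated support. The nominal concentration is therefore not assured at use. This rests on the wording alone and needs no assumption about decay.

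The effect on results is conditional and cannot be sized from the protocol. It requires that concentration falls after 6 hours and, for comparisons between concentrations, that solution age varies between participants. The likely harm would then be added noise between arms 0.1 point apart and possibly a weaker contrast with distilled water. It would be too strong to conclude that concentrations do fall or that an arm step is lost.

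**What to change.** - Reconcile the Storage and Dosing regimen sections to one use-by limit for the solution as given, supported by stability data. If two preparations were meant, name each one and state which limit applies to it. Which figure is right is for the sponsor to establish.
- Record the time of mixing and the time of application for each participant, unless the case report form already does so, so that use beyond the reconciled limit can be identified as a protocol deviation. Excluding such participants from the per-protocol set is optional and not needed to resolve this point.

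The cost is a short protocol correction, two time entries per participant and, depending on the limit adopted, more frequent mixing. The intention-to-treat analysis is unaffected.
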